## 5. TREATMENT OF SUBJECTS

### 5.1 Investigational product/treatment

All participants will receive a high-protein diet during the entire trial (12 consecutive weeks in total, starting the day directly after CID 2 until the day prior to CID3). This diet will consist of 25 energy percentage (E%) protein, 30E% fat and 45E% carbohydrates. Proteins will be 45-50% plant-based and 50-55% animal-based, to ensure a resemblance to the current western diet consisting of mainly animal-based proteins, while simultaneously acting on the currently shifting trend in society towards more plant-based diets.

Furthermore, according to randomization, one group will receive a potato-pectin fibre mixture and the remaining participants will receive a placebo.

#### ***Potato-pectin fibre mixture***

The potato-pectin fibre mixture showed the most positive results regarding short-chain fatty acid production in the distal colon in the TIM-2 model as described before. The fibre mixture will consist of 15 grams per day, consisting of 7.5 gram of potato fibre and 7.5 gram of pectin. The total of 15 grams will be equally divided over 3 doses, one for each meal.

#### ***Placebo***

The participants not receiving a potato-pectin fibre mixture will be provided with a placebo in an isocaloric manner, which will be maltodextrin. Maltodextrin Glucidex IT 12 (Roquette Freres, Lestrem, France) is a fully digestible carbohydrate and will be used as isocaloric compensation to the investigated fibre additive. Furthermore, maltodextrin will be comparable to the fibre in terms of taste, mouthfeel and appearance.

## **5.2 Use of co-intervention**

During the study period, participants should consume a protein-rich diet, of which the content, based on a subjects energy requirements and preferences, will be discussed individually. Participants should continue their regular behaviour in terms of physical activity and should refrain from using prebiotics, probiotics, antibiotics or other types of medication that can influence metabolism, glucose homeostasis or body weight. If participants visit a physician during the trial period, they should inform their physician of their partaking in this study.

## **5.3 Escape medication**

No great adverse events are expected. Gastrointestinal discomfort is the main expected side effect, for which paracetamol may be used, if necessary, with a maximum of 1000 milligrams four times daily. In the event of a continuous necessity of paracetamol for more than 3 consecutive days, participants should contact the investigator for additional advices. In case of diarrhoea or constipation, no additional supplement may be taken without contacting the investigator for a suitable solution.

## **6. INVESTIGATIONAL PRODUCT**

### **6.1 Name and description of investigational product(s)**

The investigated fibre mixture will consist of potato fibre and sugar beet pectin. The daily ingested amount will be 15 grams (7.5 grams of potato fibre and 7.5 grams of pectin), equally divided over three gifts. Every gift will be taken alongside the three main meals (breakfast, lunch, dinner). Both fibres are commonly used in the Western/Dutch diet and are proven to be safe in these amounts. Required safety and analysis certificates are available and can be found in the additional files (D2).

### **6.2 Summary of findings from non-clinical studies**

All relevant data on composition, safety, production and analyses can be found in additional files (D2).

### **6.3 Summary of findings from clinical studies**

All fibres have been tested for safety purposes in several experiments. See attached GRAS and safety documents (D2).

### **6.4 Summary of known and potential risks and benefits**

There are no known risks related to these dietary fibres. Potential risk or negative effects are related to gastro-intestinal discomfort as is described in chapter 9, 11 and 13. Potential benefits are clearly established in chapter 1, 2 and 11

### **6.5 Description and justification of route of administration and dosage**

The fibre mixture shall be added to each meal (breakfast, lunch, dinner) three times a day (3 x 5 gram = 15 gram in total). This mixture can be added to prepared or raw food, but must not be added before preparation of a meal in order to maintain chemical composition. By adding it to or distributing over a meal, it can be ingested easily and quickly.

### **6.6 Dosages, dosage modifications and method of administration**

The daily consumed dosage will be 15 gram (7.5 gram potato fibre + 7.5 gram sugar beet pectin), divided over 3 three doses of 5 grams. All will be added to a prepared or raw meal and will therefore be easily ingested.

### **6.7 Preparation and labelling of Investigational Medicinal Product**

The intervention and placebo supplements will be provided in sachets. These sachets will be packed by an experienced, independent researcher (i.e. research intern, PhD-candidate) in the kitchen of the Metabolic Research Unit Maastricht. Blinding will be assured by using identical sachets for either groups, with only the preparing researcher knowing the exact content. This researcher will also distribute the sachets to the participant.

All sachets will be labelled, containing the following information:

- Study name (DISTAL-study)
- Participant code
- Date and time of intake
- Expiration date

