### 3. STUDY DESIGN

The proposed study will be a double-blind, randomized placebo-controlled trial, to evaluate the effect of a potato-pectin fibre mixture on gut, metabolic, immune and brain health by optimizing saccharolytic and proteolytic fermentation. Individuals aged 30-75 years with overweight or obesity ( $\text{BMI} \geq 28 \text{ kg/m}^2 < 40 \text{ kg/m}^2$ ) and impaired fasting glucose (defined as fasting glucose 5.6-6.9 mmol/l or HbA1c 42-47 mmol/mol) or insulin resistance ( $\text{HOMA-IR} > 1.85$ ) will be included in the study.

All visits regarding this study will take place at the facilities of the department of human biology or the Metabolism Research Unit Maastricht of Maastricht University, or at the clinical facilities of Maastricht University Medical Center+.

After the application of an individual via (e-)mail or phone (see [Chapter 4](#) for recruitment), the researcher will contact the potential participant by email or phone to provide additional information regarding the study, answer questions and determine possible eligibility, after which a week of consideration will be given. After a week, the potential participant will be contacted again and, if they are still interested in participating, a screening visit will be planned.

The first visit to our facilities will consist of the following components:

- Checking an individual's wellbeing, medical history and determining eligibility and safety of participation.
- Signing informed consent
- Measuring vital parameters and body measurements (body weight, length, waist-to-hip ratio, systolic and diastolic blood pressure)
- Taking blood samples to determine eligibility based on specific inclusion criteria (20ml to determine glucose, insulin, ALAT, creatinine, HbA1c)

The participant will visit our facilities after a >10h overnight fasted state.

All eligible participants will be equally randomized over the two arms (potato-pectin fibre mixture vs placebo) with stratification for age, sex and HbA1c (see [Chapter 8.2](#)). The entire trial period after screening and randomization will take 13 weeks, which will be explained in more detail below.

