#### Intervention period

This randomized clinical trial with the primary outcome tissue-specific insulin sensitivity has a placebo-controlled, double blind, randomized parallel design, which allows evaluation of the role of a fibre mixture against the background of a high protein diet on host metabolism in male and female adult volunteers with overweight/obesity and impaired glucose homeostasis.

The approach is as follows:

1. Preceding this human intervention trial, a pilot study already has been performed to screen for the most optimal fibre mixture increasing distal colonic saccharolytic fermentation (and thus SCFA production) and inhibiting proteolytic fermentation. Faeces have been collected in 13 human volunteers with insulin resistance and overweight. The pooled faecal microbiota has been inoculated in TIM-2 to analyse SCFA and BCFA production after addition of different fibres or fiber combinations in a 24-h protocol against the background of a high-plant based protein mixture (which was comparable to the protein ratio as proposed in the human trial). The fibre mixture that resulted in the highest microbial SCFA production in the part of TIM-2 that represented the distal colon *in vitro* will be supplemented in the *in vivo* study. The hereby defined fibre mixture is composed out of potato and pectin fibres.
2. After randomization, the 12-week impact of a potato-pectin fibre mixture on tissue-specific insulin sensitivity will be determined in a randomized, double blind, parallel designed study.

Before the start of the intervention, participants will visit our facilities for the first clinical investigation days (CID 1 and 2). These days consist of the following test: (see [Chapter 8.3 Study procedures](#) for detailed description of the tests)

- Providing stool samples by participant
- Taking skeletal muscle and adipose tissue biopsies
- Performing two-step hyperinsulinemic-euglycemic clamp
- Performing indirect calorimetry during the clamp
- Performing gut permeability tests by intake of specific sugars dissolved in water and analysis of urine samples
- Conducting Functional Magnetic Resonance Imaging to study food-reward-related brain activity
- Conducting a DEXA scan to determine body composition
- Filling in questionnaires and performing neuropsychological tests
- Food diaries will be filled in prior to CID 1.
- Distributing and explaining of assigned intervention (a potato-pectin fibre mixture or placebo)

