After CID 1, participants will be provided with a standardized meal. This meal needs to be consumed at home on the evening before CID 2 *ad libitum*. Afterwards, they should remain

fasted until the hyperinsulinemic-euglycemic clamp on CID 2. CID 2 will take place at least 2 days and preferably within 2 weeks after CID 1. In total, participants will visit the university after an overnight fast in week 6 and on all four CIDs.

After the 12 weeks of intervention, two additional CIDs (CID 3+4) will take place, which are similar to CID 1+2, respectively.

After completing the screening and CID 1+2, the intervention will consist of either a dietary supplement or a placebo which will have to be taken thrice daily during 12 consecutive weeks. Furthermore, all participants will receive a background diet high in protein 25EN% protein mixture, 30EN% fat, and 45EN% carbohydrates. Protein content will consist for 45-50% out of plant-based protein and for 50-55% out of animal-based proteins. The protein-rich products will be consumed during breakfast and dinner. The fibre mixtures and control product can be easily consumed with protein-rich food. The exact diet composition will be discussed individually to establish a diet suited to the participants' needs and taste. The energy requirements for this diet will be estimated using indirect calorimetry based on resting energy expenditure and an activity factor of 1.5.

Both the participants and investigators will be blinded to the treatment. The study is designed to study the dietary fibre effects against the background of a high protein diet independent of any diet or exercise intervention.

In week 2, 6 and 9, participants will return for a short interview or will be contacted via telephone to assess their wellbeing and compliance, answer arisen questions and fill in questionnaires. Additionally, a stool and blood sample will be provided in 6. Questionnaires will mainly be filled in before and after the intervention, with the addition of SQUASH and three-day food diary in week 6, and BSS and GSRS in weeks 2, 6 and 9.

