### **6.8 Drug accountability**

All supplement will be shipped to Maastricht University in a safe and recognizable way as designed by the manufacturer and will be stored at the Metabolic Research Unit Maastricht at room temperature. Participants will receive all required sachets for the entire trial period (i.e. 84 sachets for a daily suppletion for 12 weeks). Participants will return all empty sachets to determine compliance and for safe disposal at our facilities. If more sachets are needed for any reason, they will be provided by an independent researcher from our facilities. All sachets will be provided in a non-transparent bag.

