### **8.2 Randomisation, blinding and treatment allocation**

Participants will be randomized to the intervention or placebo group using a validated variable block randomization using Qminim. Furthermore, minimization will be used to ensure group comparability. Factors included for minimization are age, sex and BMI.(40) Initially, CASTOR

EDC would be used for randomization and stratification for this study. After the change from stratification to minimization, however, CASTOR cannot be used since it has no minimization option. Therefore, Qminim will be used, with which there is extensive experience within our research group.

Randomization and preparing and distribution of the, for participant and investigator, unrecognizable dietary supplement (either a potato-pectin fibre mixture or placebo) will be carried out by an independent researcher. This ensures that only the independent researcher knows which subject received which supplement, while both the participant and original investigator remain blinded to the treatment. In case of emergency, the independent investigator can debind the participant(s).

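### The one person who knows the allocation also hands the sachets to participants; this needlessly exposes the participants' blind and is cheap to avoid

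*Protocol*

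**What the plan says.** Section 3 of the protocol sets the claim: "The proposed study will be a double-blind, randomized placebo-controlled trial". Under Intervention period it says who is covered: "Both the participants and investigators will be blinded to the treatment".

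Section 6.7 describes the handling of the product. The sachets are "packed by an experienced, independent researcher (i.e. research intern, PhD-candidate"). On the blind it says: "Blinding will be assured by using identical sachets for either groups, with only the preparing researcher knowing the exact content". The next sentence reads: "This researcher will also distribute the sachets to the participant". Each sachet carries the participant code.

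Section 8.2 assigns randomisation, preparation and distribution to an independent researcher and adds: "This ensures that only the independent researcher knows which subject received which supplement". The participant and the investigator in charge stay blinded.

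Section 8.3.14 puts the hand-over at the end of CID 2 and says that it is blinded for participant and investigator. The list for CID 1 and 2 in section 3 includes: "Distributing and explaining of assigned intervention (a potato-pectin fibre mixture or placebo"). It does not name who does this. Section 6.8 has an independent researcher supply extra sachets if needed, and states: "All sachets will be provided in a non-transparent bag". Section 12.1 denies those who run the experiments and analyses access to the randomisation list, and gives the principal investigator sealed envelopes for emergencies.

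**The concern.** A blind protects participants only as far as nobody who knows the allocation can signal it to them. Here the one person who knows is the person who meets each participant to deliver the product. Someone who knows the arm can, without intent, convey what to expect or encourage one group more than the other.

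The team's expectations are plain. Section 13.1 anticipates only benefit from the fibre mixture and names gastrointestinal complaints as its possible side effects. Those are the complaints that participants then rate themselves. The GSRS and Bristol stool scale are secondary endpoints in 8.1.2, and wellbeing and stress are other parameters in 8.1.3. Supplement compliance is judged from returned empty sachets (6.8), which show that a sachet was emptied but not that its content was eaten. An adherence difference produced by cues at hand-over could therefore pass unnoticed.

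**Working it through.** No figure in the protocol depends on this point, so there is nothing to compute. The check is a comparison of who knows the allocation with who meets the participant.

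1. **Who knows the content?** In 6.7, only the researcher who prepares the sachets. In 8.2, only the independent researcher, who also randomises and prepares. Both sections describe the same role.

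2. **Who delivers?** Section 6.7 says that the preparing researcher does. Section 8.2 gives distribution to the independent researcher. The two sections agree, so this is a planned arrangement and not a slip of wording.

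3. **Does anything separate that person from the participant?** The stated safeguards are:
   - identical sachets (6.7);
   - a non-transparent bag (6.8);
   - a hand-over that is blinded for participant and investigator (8.3.14);
   - no list access for experimenters and analysts (12.1).

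   The first two conceal the product. The third states the aim, but does not put a different person at the hand-over. The fourth protects measurement and analysis. None places a blinded person between the unblinded researcher and the participant, and none limits what may be said. The sealed envelopes in 12.1 add no second unblinded person while they stay sealed.

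4. **How much contact is documented?** One hand-over per participant is certain, so 44 at the planned sample size. Two further contacts are left open. Section 3 does not say who explains the product, and 6.8 speaks of an independent researcher for resupply without saying whether it is the same person.

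5. **Is the contact needed?** No. The sachets are identical, coded per participant and bagged out of sight, so someone who does not know the content can hand them over. Blinded staff already see participants on CID 2. Emergency unblinding (8.2, 12.1) does not depend on routine contact by the unblinded researcher.

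6. **What would change in the design?** Moving the hand-over leaves sample size, alpha, power and visit schedule as they are.

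**The case against.** The strongest reply is that the protocol does what it says. Its definition of double-blind covers participants and the investigator, and a knowing but independent third person fits within it. A reader might infer from the double-blind label that sections 6.7 and 8.2 contradict the design, or that the blind is broken. The documents support neither: the definition is met, and no text shows that participants learn their arm.

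A reader might also assume that the unblinded researcher instructs participants, answers their questions, resupplies them and guides the diet. That goes beyond the text. Section 6.7 gives this person distribution only. Who explains and who resupplies is not fixed, and the contacts in weeks 2, 6 and 9 are not assigned to this person. The diet is composed with a dietician (8.3.14), so a route through diet adherence would be conjecture.

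The primary endpoint is a clamp measurement, taken by people without list access and after a single documented hand-over that follows the baseline assessments. The self-reported outcomes are secondary or other parameters, and section 4.4 treats secondary outcomes as exploratory. All of this stands and limits the weight of the point.

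Keeping product handling away from assessors also has some value. Sealed, identical, coded sachets tell blinded staff little, however, so that does not outweigh the benefit of removing the contact.

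What the reply does not remove is the core: independence does not cancel knowledge of the allocation, and the contact serves no stated purpose.

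**Conclusion.** The point holds as an avoidable weakness in the blinding procedure. Sections 6.7 and 8.2 have the only person who knows the allocation deliver the product to all participants. That leaves open a route by which cues could reach expectation, supplement adherence and self-reported outcomes (GSRS, Bristol stool scale, stress, wellbeing). The direct route to the clamp result is limited by 12.1; an indirect one through supplement adherence remains possible.

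Its size cannot be derived. A reader might be tempted to assume an adherence difference between arms and scale the 2.86 µmol/kg/min planning difference of section 4.4 by it. The protocol gives no adherence figure and no dose-response, and 2.86 is a planning value and not an observed effect, so such a number would have no basis.

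The conclusion rests on two assumptions: that distribution in 6.7 and 8.2 means hand-over in person, as their wording suggests, and that no procedure outside the protocol restricts what is said. It is a cheap improvement worth making, not a flaw that invalidates the trial.

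**What to change.** Amend four sections so that they tell the same story.

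- **6.7 and 8.2:** the independent researcher randomises, packs, codes and seals the identical, participant-coded sachets in the non-transparent bag, and has no routine contact with participants.
- **8.3.14:** a staff member who does not know the allocation hands over the sealed bag at the end of CID 2 and explains its use. The matching item in section 3 can name the same role.
- **6.8:** the independent researcher prepares any resupply in the same sealed form, and a blinded staff member gives it out.

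The emergency unblinding route stays as it is.

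The cost is a few sentences, with no change to sample size, visits or measurements. There are two small downsides. Bags must be ready before CID 2 ends, and blinded staff take on the hand-over. Where existing staffing allows, this should preferably be someone who does not run that participant's outcome assessments.

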### **6.8 Drug accountability**

All supplement will be shipped to Maastricht University in a safe and recognizable way as designed by the manufacturer and will be stored at the Metabolic Research Unit Maastricht at room temperature. Participants will receive all required sachets for the entire trial period (i.e. 84 sachets for a daily suppletion for 12 weeks). Participants will return all empty sachets to determine compliance and for safe disposal at our facilities. If more sachets are needed for any reason, they will be provided by an independent researcher from our facilities. All sachets will be provided in a non-transparent bag.

## **7. NON-INVESTIGATIONAL PRODUCT**

### **7.1 Name and description of non-investigational product(s)**

Insulin and glucose will be used for the hyperinsulinemic-euglycemic clamp, which are regularly used products in clinical settings and are used as the golden standard for determination of insulin resistance. Lidocaine for local anesthesia is also regularly used in both clinical and research settings.

All are safe for human use. Further details can be found in attachment D2.

Gut permeability will be assessed with the Multisugar test (MS), performed by using specific orally administered sugars (~~4-gram sucrose~~, 1 gram lactulose, 1 gram sucralose, 1 gram erythritol, 0.5 gram rhamnose) which are all either commonly used sugars, European Food Safety Authority-approved artificial sweeteners or found to be safe for administration by previous studies.(39)

### **7.2 Summary of findings from non-clinical studies**

Not applicable

### **7.3 Summary of findings from clinical studies**

The usage of the multisugar test has been proven safe and effective to determine gut permeability.(39) All sugars were tested by Basic Pharma (Geleen, the Netherlands) to ensure safe oral human consumption. Furthermore, this test has been used successfully by our department before on multiple occasions, yielding reliable results without any adverse effects.

